# VR-SOAP, a modular virtual reality treatment for improving social activities and participation of young people with psychosis: a study protocol for a single-blind multi-centre randomized controlled trial

**DOI:** 10.1186/s13063-023-07241-z

**Published:** 2023-04-15

**Keywords:** Social functioning, Psychotic disorder, Virtual Reality, Personalized Treatment

## Abstract

**Background:**

Young people with a psychotic disorder have the same social goals as their healthy peers, but their social networks are smaller, they participate less often in leisure activities and are less successful in work and education. Causes of these problems are multifaceted, but culminate in difficulties with interacting in daily life social situations. Current treatments have only moderate effects on social functioning and often target one specific domain. Virtual reality (VR) has the potential to improve the treatment of social interaction difficulties. We developed a modular VR treatment for social functioning and participation (VR-SOAP). In this study, the effect of this intervention will be investigated in a randomized controlled trial (RCT).

**Methods:**

A total of 116 participants (age 18–40) with a DSM-5 diagnosis of schizophrenia spectrum or other psychotic disorder and problems with social functioning will be recruited from mental healthcare institutes in the Netherlands. Participants will be randomized to the experimental condition (VR-SOAP) or active VR control condition (VRelax). VR-SOAP consists of 14 sessions and 5 modules addressing causes of impaired social functioning: four optional modules (1–4) and one fixed module (5). Vrelax consists of 14 sessions that entail psychoeducation, stress management, relaxation techniques, and the exploration of relaxing environments in VR. Primary outcomes are quantity and quality of social contacts, leisure activities and social participation, measured with the experience sampling method (ESM). Secondary outcomes are psychiatric symptoms, social behaviour, social cognition, self-esteem, self-stigma and paranoid thoughts. Treatment effects will be compared at pre-treatment (baseline), post-treatment and at 6-month follow-up.

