#### Primary outcome

##### Quantity and quality of social contacts, leisure activities and social participation

Three domains of social functioning are measured with the experience sampling method (ESM). Participants will complete ESM diaries at semi-random moments, prompted by a signal on their phone, five times a day for 2 weeks. Items are scored on a Likert scale ranging from 0 (not at all) to 7 (very) or as multiple-choice questions.

The diary consists of 35 items and will take 2–3 min to complete. Each time the participant is asked whether he or she is or has engaged in any (social) activity, at that particular moment, and since the previous questionnaire. If the participant is engaged in a (social) activity, the participant is asked additional questions, e.g. I feel accepted by this company. The diary parallels the five modules such that different underlying processes targeted in VR-SOAP are assessed (e.g. we expect the item: “I find this activity pleasurable”, to be associated with negative symptoms.).

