### Statistical analyses

All analyses will be intention to treat. The intention-to-treat analysis will include all participants who have given their informed consent and have been randomized to a group after the baseline assessment. Descriptive statistics will be calculated for all clinical and outcome variables as well as for sociodemographic variables. Means that differ significantly at baseline between groups will be added as a covariate to the analysis. For each domain of the primary outcome variable, mean total scores are calculated based on all 70 scores (5 times a day × 14 days = 70 scores). Multilevel mixed-model regression analysis will be used for the analysis of the primary outcome (ESM). Repeated assessments will be nested within participants and all models will include a random intercept for participant. The method of estimation is maximum likelihood and the covariance structure independent. Treatment effects are evaluated with group (VR-SOAP or VRelax) × time (baseline, end of treatment, follow-up) interaction terms. Measures taken after treatment and follow-up will be evaluated separately.

A mediator analysis will be conducted to identify the underlying processes of change in the primary outcome. The primary analysis will be followed up with sensitivity analysis on completers, i.e. patients who completed 12 or more sessions. In case of missing data, participants will be included in the analysis with the exclusion of the missing datapoint. If the overall proportion of missing questionnaire items was less than 5% and the participant had less than one missing item for every ten items, their mean at that specific time point was used to impute the missing data.

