#### Sample size calculation

Mean effect sizes of current interventions on social functioning are around *d* = 0.5 [52]. With the G-power software package, the effect size is calculated based on an estimated effect size on the primary outcome of 0.5 [13, 53, 54], two groups, statistical power of 0.8, alpha of 0.05 and a standard deviation of 0.9. The required sample size of 102, with a correction for an estimated 13% [55] drop-out, amounts to *N* = 116.

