## Discussion

The primary objective of this study is to evaluate the effect of a novel, modular VR intervention for improving social interaction difficulties in people with a psychotic disorder. It is hypothesized that the VR-SOAP group will show greater improvements in the quantity and quality of social contacts, leisure activities and social participation than the VRelax group at post-treatment and follow-up and we expect that these improvements are mediated by changes in underlying processes.

Although NICE guidelines consider social functioning as one of the “critical” outcome measures, current approaches have shown only moderate effects to this end [11–13]. Given that in the Netherlands alone around 100,000 people are receiving treatment in a mental health care setting for a psychotic disorder, many of whom have problems with social interactions [57], more effective interventions to improve social functioning are highly needed.

If VR-SOAP proves to be effective, it provides young adults with a psychotic disorder much-needed support to engage in social activities and to participate in society. Additionally, since the treatment consists of multiple modules targeting different transdiagnostic factors this trial might provide input for new treatments to improve social functioning in a range of symptoms and disorders, e.g. mood, autism spectrum and anxiety disorders.

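### Three primary ESM domain scores are each evaluated at two time points, with no primary time point or success rule, while the trial is sized for one test at alpha 0.05

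*Protocol article*

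**What the plan says.** All references are to the protocol article.

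- **Abstract, Methods.** The primary outcomes are plural: "Primary outcomes are quantity and quality of social contacts, leisure activities and social participation, measured with the experience sampling method (ESM".
- **Measures, Primary outcome.** "Three domains of social functioning are measured with the experience sampling method (ESM".
- **Statistical analyses.** Each domain has its own score: "For each domain of the primary outcome variable, mean total scores are calculated based on all 70 scores". No composite across domains is described. The effect is tested through an interaction: "Treatment effects are evaluated with group (VR-SOAP or VRelax) × time (baseline, end of treatment, follow-up) interaction terms". The next sentence adds: "Measures taken after treatment and follow-up will be evaluated separately".
- **Discussion.** The hypothesis is that VR-SOAP will show "greater improvements in the quantity and quality of social contacts, leisure activities and social participation than the VRelax group at post-treatment and follow-up".
- **Sample size calculation.** The outcome is now singular: "the effect size is calculated based on an estimated effect size on the primary outcome of 0.5". The other inputs are "two groups, statistical power of 0.8, alpha of 0.05 and a standard deviation of 0.9". The result is 102, raised to 116 for 13% drop-out.

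The article states no primary domain, primary time point, order of testing, division of alpha or number of results that must be significant.

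**The concern.** The sections describe different trials. The outcome and analysis sections set up three primary scores at two separately evaluated time points. The sample size section sets up one primary outcome and one test.

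Two things are at stake. First, the error rate and power of the primary claim are unknown until it is said which result, or which set of results, establishes efficacy. The stated alpha and power fit only a single test that the article does not identify. Second, domain and time point could be given emphasis after the data are seen, because nothing fixes them beforehand.

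This goes beyond a multiplicity method left to a SAP. The sample size reproduces only with an undivided alpha, so any later correction over domains or time points would contradict the stated power unless that power is restated.

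**Working it through.** **1. The plan's own figure.** Inputs from Sample size calculation: difference 0.5, SD 0.9, alpha 0.05, power 0.8. With the two-sided normal formula:

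n per arm = 2 × (1.960 + 0.842)² × 0.9² / 0.5² = 50.9, so 51 per arm and 102 in total.

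This matches exactly. Sidedness is not stated, and a one-sided t-test with a standardized d of 0.5 also gives 102. Both routes use one test at an undivided alpha of 0.05. Drop-out: 102 × 1.13 = 115.3, so 116.

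**2. Number of primary tests.** Three domain scores × two time points = 6.

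**3. Error rate if any one test suffices, each at two-sided 0.05.** For independent tests:

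- either direction: 1 − 0.95⁶ = 26.5%
- in favour of VR-SOAP only: 1 − 0.975⁶ = 14.1%

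The article gives no correlations between the tests, so a range is needed. Simulated normal statistics with a common correlation give:

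| Correlation | Either direction (nominal 5%) | Favouring VR-SOAP (nominal 2.5%) |
|---|---|---|
| 0 | 26.5% | 14% |
| 0.3 | 24% | 12% |
| 0.5 | 21% | 10% |
| 0.7 | 16% | 8% |
| 0.9 | 11% | 5% |

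Letting domains and time points have different correlations changes little: 0.5 between domains with 0.5 or 0.7 between time points gives 22% or 20% in either direction.

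**4. Error rate and power if all six must succeed.** Type I error is at most 5%, because the joint claim requires every single test to reject. If each test has power 0.80, joint power lies between 0.80⁶ = 0.26 (independent) and 0.80 (perfectly correlated). The stated 0.8 is therefore only the upper limit.

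**5. Power with Holm over three domains at one time point.** The first Holm step uses 0.05/3 = 0.0167, with a two-sided critical value of 2.394. With 51 per arm on 0.5/0.9, the expected test statistic is (0.5/0.9) × √(51/2) = 2.805.

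| Basis | Single test at 0.05 | First Holm step |
|---|---|---|
| 0.5/0.9, normal | 0.80 | 0.66 |
| 0.5/0.9, t-test | 0.79 | 0.64 |
| d = 0.5, t-test | 0.71 | 0.54 |

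For power 0.80 at 0.0167 on 0.5/0.9 (normal), 136 evaluable participants would be needed, or 136/0.87 = 156.3, so 157 with 13% drop-out.

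**The case against.** The strongest reply is that no inflated error rate has been shown. Alpha 0.05 appears only under Sample size calculation, and Statistical analyses gives no threshold. An article condenses a fuller protocol, and a SAP may set a multiplicity rule. The Discussion joins all domains and both time points with the word and. If that is the success rule, type I error is controlled. This stands as far as it goes, and it is why the error rates above are conditional. It does not remove the conflict: the Discussion states a hypothesis, not a decision rule, and the sample size is not calculated for joint success.

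Three stronger readings are tempting, and the article does not support them.

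- **A false claim of efficacy has a probability of 21% to 26% or more.** Those figures count rejections in both directions, including results that favour VRelax. Nor is 21% a floor: it falls to 16% at correlation 0.7 and 11% at 0.9. The post-treatment and follow-up contrasts within a domain share participants and baseline, so high correlation is plausible for those pairs.
- **Quantity and quality make twelve tests.** Statistical analyses describes one mean total score per domain, so six is the count that the text supports.
- **Any one positive test would be taken as proof.** The article states no such rule. It also does not exclude one.

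The count could also be lower. One interaction test per domain across all time points would give three tests, with two-sided error of 11% to 14% for correlations 0.7 to 0. The sentence on separate evaluation makes six the likelier reading.

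**Conclusion.** The point holds as a conflict in the stated text: six primary tests with no primary time point or success rule, against a sample size for one test.

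Its size depends on the missing rule. If any one unadjusted two-sided test at 0.05 suffices, the familywise error is about 16% to 26% for correlations 0.7 to 0 (11% at 0.9). In favour of VR-SOAP it is about 8% to 14% (5% at 0.9), against 2.5%. That is at least twice nominal in every case examined. If all six must succeed, type I error is at most 5% and power is the problem. Under either rule, the stated alpha and power together do not describe the planned primary claim.

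The ranges assume approximately normal test statistics with a common correlation, because the article reports none. The per-test level of 0.05 is inferred from the sample size section.

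**What to change.** Before unblinding, state the following in the protocol or SAP:

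1. One primary time point, for example post-treatment (T1), with follow-up (T2) as key secondary. The article does not determine this choice, since it hypothesizes benefit at both.
2. The three domain scores at that time point are tested with Holm at a familywise two-sided 0.05.
3. Efficacy is claimed only for domains that pass.
4. Power per domain at the first Holm step is given beside the single-test figure: about 0.64 to 0.66 against 0.79 to 0.80 on 0.5/0.9, or 0.54 against 0.71 if 0.5 is a standardized d. The basis used should be named.

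The change takes a few sentences and no new data. Its cost is a lower stated power per domain at the planned size. An explicit rule that all tests must succeed, or a fixed testing sequence, would also resolve the conflict, provided that power is restated to match.

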**Discussion:**

If VR-SOAP proves to be effective, it provides therapists with a much-needed tool to improve social functioning of young adults with a psychotic disorder. Additionally, since the treatment consists of multiple modules targeting different transdiagnostic factors, this trial might provide input for new treatments to improve social functioning in a range of symptoms and disorders, e.g. mood, autism spectrum and anxiety disorders.

**Trial registration:**

On the 10th of November 2021, this trial was registered prospectively in the Dutch Trial Register as NL9784.

## Background

Young people with a psychotic disorder have the same social goals as their peers [1, 2], but their social networks are smaller, they participate less often in social leisure activities and they are less successful in their work and educational pursuits [2–5]. A reduction in the quantity and quality of social contacts, leisure activities, and participation in society are core aspects of impaired social functioning. In turn, reduced social functioning among young people with psychosis is associated with a lower quality of life [2], depressive symptoms and social anxiety symptoms [6]. Estimates of a good functional outcome after a first episode of psychosis range between 17 and 45% [7, 8]. Moreover, 20 years after their first episode of psychosis, the majority of patients still have impaired social functioning [9]. Since social functioning impairments have a major and persistent impact on a patient’s quality of life and come with a large societal cost [10], effective treatment is vital.

In recent decades, several interventions have been developed to improve the social functioning of patients with a psychotic disorder, e.g. social skills training, social cognition training and cognitive behavioural therapy. However, these approaches have shown only moderate effects on social functioning [11–13]. As they generally target a single aspect, they may not sufficiently capture the multifaceted nature of social functioning problems in psychosis.

Based on the literature, we identified the main determinants of impaired social functioning in patients with recent onset psychosis [14, 15]. For example, negative symptoms, in particular impaired motivation and pleasure, are a barrier to successful engagement in social activities [16–18]. Additionally, social cognition problems are strongly related to impaired social functioning [19]. Furthermore, paranoid ideations and social anxiety can result in avoidance and safety behaviours, complicating social functioning [20, 21]. Likewise, low self-esteem and self-stigma make social interactions challenging [22]. Importantly, patients often have reduced social skills [14, 23]. These causes jointly culminate in difficulties interacting in daily life social situations. Therefore, any treatment targeting social functioning problems should identify and address an individual’s array of multiple overlapping and interrelated causes.

Recently, there has been an interest in developing personalized interventions. Among these personalized interventions are modular treatments. Modular treatments consist of several interconnected, yet independent modules [24]. A literature review of interventions for individuals at risk for psychosis emphasized the need for modular treatments for young people with psychosis, as these treatments could effectively meet their varying individual needs [25]. Preliminary results of a recently developed modular treatment for persecutory delusions in psychosis were promising: patients were satisfied with the treatment and believed that it helped [26].

Another challenge in traditional treatments for social functioning is generalizability, as it is difficult for patients to implement the skills acquired during therapy into their daily lives [23, 27]. Skills should be trained in an environment similar to everyday life [27]. However, this can be time-consuming and is not always possible in a conventional clinical setting. Virtual reality (VR) offers this possibility and has great potential to improve the training of social functioning among patients with psychosis [28–31]. With VR, patients can repeatedly practice social interactions in a simulated three-dimensional real-life setting. Using VR, real-life emotional and behavioural responses can be evoked and behaviour can be practiced in a safe and controlled setting [23, 28]. Preliminary studies have indicated that VR treatment for social skills among individuals with psychosis is feasible and may be effective [23, 32].

To address both the multifaceted nature of each individual’s social functioning problems and the concern of generalizability, our lab in collaboration with persons with lived experience, developed a Virtual Reality Treatment for Social Activities and Participation (VR-SOAP); a personalized, modular VR treatment to promote social activities and participation among young people (18–40 years) with psychosis. VR-SOAP consists of various optional modules that target several processes that are thought to underlie impaired social functioning [33].

This paper outlines the study protocol of a randomized controlled trial to investigate whether VR-SOAP is superior to an active control condition (Vrelax). The primary aim of the study is to test whether VR-SOAP improves the quantity and quality of social contacts, leisure activities and social participation using the Experience Sampling Method (ESM). Second, the study will investigate whether the effects of VR-SOAP are mediated by changes in the contributing causes of impaired social functioning (i.e. negative symptoms, social cognition problems, paranoid ideations, low self-esteem, self-stigma, and social skills).

## Methods/design

Ethics approval for the study was obtained from The Medical Ethics Review Board of the University Medical Center Groningen (number NL69628.042.21). The study is registered in the Netherlands Trial Register (number: NL9784).

### Participants/setting

To reach the desired sample size, participants will be recruited from multiple mental healthcare centres in the Netherlands (University Center of Psychiatry of the University Medical Center Groningen, GGZ Drenthe, Dimence, Mentrum, KieN-VIP, Altrecht and GGZ Rivierduinen). Patients receiving ambulatory care will be included. Eligible and interested participants will be referred by their clinician and contacted by researchers.

Inclusion criteria are:□ DSM-5 [34] diagnosis of schizophrenia spectrum or other psychotic disorder determined by a semi-structured diagnostic interview.□ Reduced quantity or quality of social contacts, leisure activities or social participation, according to the treating clinician or patient.□ Age 18–40 years.

Exclusion criteria are:□ IQ < 70 estimated by treating clinician.□ Insufficient command of the Dutch language.□ Photosensitive epilepsy.

If the diagnosis of a schizophrenia spectrum or other psychotic disorder has not been established according to DSM-5 criteria with a semi-structured interview in the past 5 years, the Mini-SCAN [35] will be administered to confirm clinical diagnosis. The interview will target psychotic episodes over a lifetime period.

Participants can receive a maximum of 40 euros for the three measurements and will be reimbursed for any travel expenses during the assessment.

### Design

See Fig. 1 for the CONSORT flow diagram. The study is a multi-centre single-blind randomized controlled trial (RCT) with two conditions: the experimental VR treatment (VR-SOAP) and VR relaxation (VRelax) as an active control condition.

**Fig. 1 Fig1:**
[figure not shown]
Flowchart of study

Both groups continue to receive treatment as usual (TAU) during the study, which can include antipsychotic medication and contacts with a psychiatric nurse and/or psychiatrist. Both groups participate in an assessment before the start of treatment (T0), at post-treatment (T1) and 6 months after the end of treatment (T2).

### Interventions

#### VR-SOAP (experimental condition)

VR-SOAP is a VR treatment of 14 individual weekly sessions of 60 min with a psychologist. The sessions are provided with a detailed treatment protocol and session forms to ensure treatment integrity. Therapists who hold at least a master’s degree in clinical psychology and a basic qualification to provide cognitive behavioural therapy (CBT) deliver VR-SOAP.

VR-SOAP consists of five modules (Fig. 2) that address the identified various causes of impaired social functioning: four optional modules (1–4) and one fixed module (5). In sessions 1–2, the patient and therapist discuss the baseline assessment (T0) and formulate goals concerning social contacts, leisure activities and/or social participation. After session 2, the patient and therapist select two of the optional VR modules (4 sessions each), depending on a combination of the perceived causes of the patient’s social interaction difficulties, the results of the baseline assessment and the patient’s goals:Module 1: Domain—Negative symptoms; Treatment components—behavioural activation and planning in social situations, demoralization, training attention control and information processing.Module 2: Domain—Social cognition; Treatment components—recognizing facial emotions, interpreting social situations, mentalizing.Module 3: Domain—Paranoid ideations and social anxiety; Treatment components—behavioural experiments testing harm expectancies, exposure exercises, dropping safety behaviour.Module 4: Domain—Self-esteem and self-stigma; Treatment components—improving positive self-image in interactions, practicing disclosure of mental illness.

